# Favipiravir and/or nitazoxanide: a randomized, double-blind, placebo-controlled trial of early therapy in COVID-19 in health workers, their household members, and patients treated at IMSS (FANTAZE)

**DOI:** 10.1186/s13063-022-06533-0

**Published:** 2022-07-22

**Keywords:** COVID-19, Antivirals, Combination therapy, Early treatment, 2×2 design, Favipiravir, Nitazoxanide, Placebo-controlled trial, Protocol, Randomised controlled trial

## Abstract

**Background:**

The 2020 pandemic of SARS-CoV-2 causing COVID-19 disease is an unprecedented global emergency. COVID-19 appears to be a disease with an early phase where the virus replicates, coinciding with the first presentation of symptoms, followed by a later ‘inflammatory’ phase which results in severe disease in some individuals. It is known from other rapidly progressive infections such as sepsis and influenza that early treatment with antimicrobials is associated with a better outcome. The hypothesis is that this holds for COVID-19 and that early antiviral treatment may prevent progression to the later phase of the disease.

**Methods:**

Trial design: Phase IIA randomised, double-blind, 2 × 2 design, placebo-controlled, interventional trial.

Randomisation: Participants will be randomised 1:1 by stratification, with the following factors: gender, obesity, symptomatic or asymptomatic, current smoking status presence or absence of comorbidity, and if the participant has or has not been vaccinated. Blinding: Participants and investigators will both be blinded to treatment allocation (double-blind).

**Discussion:**

We propose to conduct a proof-of-principle placebo-controlled clinical trial of favipiravir plus or minus nitazoxanide in health workers, their household members and patients treated at the Mexican Social Security Institute (IMSS) facilities. Participants with or without symptomatic COVID-19 or who tested positive will be assigned to receive favipiravir plus nitazoxanide or favipiravir plus nitazoxanide placebo. The primary outcome will be the difference in the amount of virus (‘viral load’) in the upper respiratory tract after 5 days of therapy. Secondary outcomes will include hospitalization, major morbidity and mortality, pharmacokinetics, and impact of antiviral therapy on viral genetic mutation rate. If favipiravir with nitazoxanide demonstrates important antiviral effects without significant toxicity, there will be a strong case for a larger trial in people at high risk of hospitalization or intensive care admission, for example older patients and/or those with comorbidities and with early disease.

**Trial registration:**

ClinicalTrials.govNCT04918927. Registered on June 9, 2021.

## Administrative information

Note: the numbers in curly brackets in this protocol refer to SPIRIT checklist item numbers. The order of the items has been modified to group similar items (see http://www.equator-network.org/reporting-guidelines/spirit-2013-statement-defining-standard-protocol-items-for-clinical-trials/).

## Introduction

### Background and rationale {6a}

In viral infections such as influenza, it is well recognized that early antiviral therapy is associated with improved clinical outcomes. Using drugs with differing modes of action is a fundamental principle of antimicrobial chemotherapy and is used across the spectrum of infectious diseases (for example in HIV, tuberculosis, multi-drug resistant bacteria and invasive fungal disease).

The antiviral drug favipiravir is active against a broad range of viruses and has shown promising results in COVID-19 disease in two small Chinese studies [1, 2]. The drug works similarly to remdesivir (another promising treatment for COVID-19), but unlike remdesivir (which is intravenous) it has a well-established and currently available oral formulation with a good safety profile. Furthermore, both Royal Free Hospital and Great Ormond Street Hospital (London) involved in this trial are amongst the only UK groups with direct clinical experience of this drug, having successfully used favipiravir to treat other viral infections.

The results of the early studies [1, 2] on favipiravir in COVID-19 urgently need to be confirmed or refuted in a high-quality placebo-controlled trial.

Another antiviral with potential activity in COVID-19 is nitazoxanide. Nitazoxanide and its active metabolite, tizoxanide, are active against a variety of bacteria and have also been found to have activity against many DNA and RNA viruses. Nitazoxanide acts as an antiviral at the step after favipiravir in that it inhibits blocks maturation of the viral nucleocapsid N protein and therefore viral assembly [3]. It has also been suggested that nitazoxanide may have non-specific beneficial effects including innate immune system boosting and damping late immune and inflammatory responses [3, 4].

Favipiravir and nitazoxanide have different mechanisms of action so given together are likely to act at least additively, and possibly synergistically, providing a strong rationale for a trial which examines combination therapy.

Health workers are at high risk of acquiring SARS-CoV-2 infection, as already demonstrated in areas which have experienced significant outbreaks. Apart from the risk of severe illness and death in the workers themselves and their household members, this phenomenon also impacts staffing levels in critical systems. There is an urgent need to study subjects who have recently developed symptoms or have recently been tested positive with or without symptoms, and who can be sampled frequently to understand changes in viral load. Conducting a trial including, but not limited to, health workers and their household members can help fulfilling this need. In addition to being at great need for therapeutic interventions, this population provides the ideal cohort to collect detailed trajectory data on early disease and understand how pharmacological interventions may affect this.

The design of the FANTAZE trial is based on the FLARE trial [5] conducted in the UK in 2020–2021.

### Objectives {7}

The primary objective of this trial is to assess whether early antiviral therapy with favipiravir + nitazoxanide is associated with a decrease in viral load compared with favipiravir alone.

Secondary objectives will include hospitalization, major morbidity and mortality, pharmacokinetics, and impact of antiviral therapy on viral genetic mutation rate.

### Trial design {8}

FANTAZE is a phase IIA randomised, double-blind, placebo-controlled, interventional trial.

## Methods: participants, interventions and outcomes

### Study setting {9}

The Mexican Institute of Social Security (IMSS) will be responsible for both the research centres where the trial will be carried out, as well as for the selection of the researchers that will participate in the trial.

The study will be carried out at the Infectious Disease National Medical Centre “La RAZA” Hospital. Participants will be recruited among health workers, their household members and patients that are diagnosed at La Raza or any of the outpatient clinics in its service area (north section of Mexico City and its suburbs).

### Eligibility criteria {10}

Participants will be considered eligible for enrolment in this trial if they fulfil all the inclusion criteria and none of the exclusion criteria as defined below.

#### Participant inclusion criteria

Health workers, their household members and patients treated at IMSS facilities with the following:Symptoms compatible with COVID-19 disease (fever >37.8°C on at least one occasion and either cough and/ or anosmia) within the first 5 days of symptom onset (date/time of enrolment must be within the first 5 days of symptom onset).Or any symptoms compatible with COVID-19 disease (may include, but are not limited to fever, cough, shortness of breath, malaise, myalgia, headache, coryza) and tested positive for SARS-CoV-2 within the first 5 days of symptom onset (date/time of enrolment must be within the first 7 days of symptom onset).Or no symptoms but tested positive for SARS-CoV-2 within the last 48 h (date/time of test must be within 48 h of enrolment).2.Male or female aged 18 years to 70 years old inclusive at screening.3.Willing and able to take daily nose swab samples.4.Able to provide full informed consent and willing to comply with trial-related procedure.

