## Statistical methods

### Statistical methods for primary and secondary outcomes {20a}

Summary of baseline characteristics, by trial arms, will be by frequency and percentage for categorical variables, and for continuous variables by mean and standard deviation (or median and inter-quartile range for non-normally distributed data).

The primary endpoint will be analysed using a linear mixed-effect model, including the main effects (each experimental treatment) as factors, and the interaction between them. Baseline values of viral load will be included for each subject and, linked within subjects using random intercept terms.

An analysis of covariance (ANCOVA) will also be performed: the ANCOVA model will use the viral load on Day 5 as the dependent variable and include the baseline value as independent variable.

Secondary endpoints include binary endpoints and continuous endpoints (note that the pharmacokinetic analysis of favipiravir and nitazoxanide is described in a separate section below).

For binary endpoints, a logistic regression will be used. The adjustment strategy will be the same as the primary endpoint.

The comparison of duration of fever following commencement of medication between trial arms will be by t-test, or non-parametric equivalent depending on the distribution of the data. Regression models will also be used to perform analyses adjusted for site (as random effect.).

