## Discussion

Two recent pre-print papers [9, 10] on the viral dynamics of SARS-CoV-2, the cause of COVID-19, provide simulations to show that viral load peaks around 3 days after symptom onset and that antiviral therapy started later than day 4 may have limited benefit. Furthermore, late antiviral therapy, once viral loads are high, risks selection for drug resistance. Therefore, there are strong grounds to believe that if antivirals are to have a place in the treatment of SARS-CoV-2, they should be given early and, if possible, within the first 7 days of symptom onset.

Both recent SARS-CoV-2 modelling papers [9, 10] suggest that drugs need to provide a minimum of 65% inhibition of viral replication, with this percentage increasing to 90% or more if therapy is initiated late, meaning a combination therapy may improve the chances of achieving sufficient viral inhibition.

Favipiravir is orally administered and well absorbed with close to 100% bioavailability [11] . The drug is metabolized to a ribosyl triphosphate form which specifically inhibits the RNA-dependent RNA polymerase without affecting host RNA and DNA polymerases, thereby rendering it a specific inhibitor of viral RNA synthesis. The highest dose used in Phase II trials, for which safety is established, and hence proposed in this trial is 1800 mg twice daily on day 1 followed by 800 mg twice daily.

Favipiravir has been used clinically in several viral infections and in some cases, the drug has been observed to induce viral mutagenesis [12]. Occasional asymptomatic elevation of liver aminotransferase levels was observed, but no serious adverse events related to the drug. Importantly, animal studies have indicated potential teratogenicity and the drug is distributed in sperm: therefore, a negative pregnancy test for all women of child-bearing potential will be required and participants instructed to use adequate contraception for the duration of the treatment and 7 days afterward [13].

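### Days since symptom onset is missing from the stated primary model, although entry runs to day 5 or day 7 and baseline load alone cannot tell a rising from a falling viral load

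*Protocol article*

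**What the plan says.** The Objectives section asks whether "early antiviral therapy with favipiravir + nitazoxanide is associated with a decrease in viral load compared with favipiravir alone". The Discussion, citing simulations in two pre-prints, says that "viral load peaks around 3 days after symptom onset and that antiviral therapy started later than day 4 may have limited benefit". The same paragraph concludes that if antivirals have a place, "they should be given early and, if possible, within the first 7 days of symptom onset".

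The inclusion criteria give three routes into the trial:

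- **Compatible symptoms without a test:** "date/time of enrolment must be within the first 5 days of symptom onset".
- **Any symptoms plus a positive test:** "tested positive for SARS-CoV-2 within the first 5 days of symptom onset (date/time of enrolment must be within the first 7 days of symptom onset").
- **Asymptomatic:** "no symptoms but tested positive for SARS-CoV-2 within the last 48 h". These participants have no onset date.

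For the primary endpoint, the statistical methods section {20a} names a mixed model with baseline viral load and random intercepts. In addition, "the ANCOVA model will use the viral load on Day 5 as the dependent variable and include the baseline value as independent variable". Baseline load is the only participant-level covariate named, and binary endpoints take the same adjustment strategy. Site appears as a random effect, in the paragraph on fever duration.

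Days since onset is in neither list of allocation factors (Sequence generation {16a}, Implementation {16c}); both lists include symptomatic versus asymptomatic. The additional analyses {20b} cover pharmacometric and viral dynamic modelling and sequencing, with no analysis by onset time.

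**The concern.** On the protocol's own account of the viral course, some participants start before the peak, some at it, and some two to four days into natural decline. Two people with the same baseline load can then have very different expected Day 5 loads, whatever their treatment. Days since onset carries that information and must already be known to apply the inclusion criteria. Leaving it out puts predictable variation into the residual and widens the confidence interval for the primary contrast.

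A second, less certain cost is dilution. If the added effect of nitazoxanide is smaller in later starters, the estimate averages over them and lies below the effect in early starters, to whom the objective refers.

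**Working it through.** **1. Why baseline load is not a substitute.** Take a peak at day 3 (Discussion), a rise of r and a decline of d log10 per day, and Day 5 falling four days after the first dose on Day 1.

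- Entry on day 1 after onset: two days of rise, then two of decline. Change = 2r − 2d.
- Entry on day 6 after onset: four days of decline. Change = −4d.
- Gap at equal baseline = 2r − 2d + 4d = 2(r + d).

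The documents give no slopes. With assumed r = 0.5 to 2 and d = 0.3 to 0.7, the gap runs from 2 × 0.8 = 1.6 to 2 × 2.7 = 5.4 log10. These are two extreme entrants without noise, so they show direction and not the average gain.

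**2. Average precision gain, by simulation.** Assumptions: uniform entry over 0–5 or 0–7 days, peak at day 3 (SD 1), the slopes above, assay plus swab SD 1, and 200,000 participants per scenario. The residual variance of Day 5 load on baseline load was compared with and without days since onset.

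| Setting | 0–5 days | 0–7 days |
|---|---|---|
| No recall error, common decline, peak-height SD 1–1.5 | about 13–36% | about 17–48% |
| Onset recall error SD 1 day, between-person decline SD 0.25 log10/day, peak-height SD 0–2 | about 2–22% | about 10–32% |

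The second row is the more realistic. Interval width scales with √(1 − cut): √0.98 = 0.99 at the low end and √0.68 = 0.82 at the high end, that is, intervals about 1% to 18% narrower. The gain arises only in symptomatic entrants. Their share is not stated, so these figures are upper limits for the whole trial.

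**3. The sample size as a frame for dilution.** 108/(1 − 0.10) = 120 reproduces the recruitment target. No SD, alpha or power is given, so the 108 cannot be reproduced. With 54 per arm, a 1 log10 difference and an assumed two-sided alpha of 0.05, SD = √(54/2) × 1/(1.96 + 0.84) ≈ 1.85 for 80% power, and √(54/2) × 1/(1.96 + 1.28) ≈ 1.60 for 90%.

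If a share f starts after day 4 and keeps a fraction k of the effect, the mean difference is 1 − f(1 − k). Both f and k are assumptions.

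| f | k | Mean difference | Power, SD 1.85 | Power, SD 1.60 |
|---|---|---|---|---|
| any | 1 | 1.0 | 80% | 90% |
| 20% | 0.5 | 0.9 | 72% | 83% |
| 20% | 0 | 0.8 | 61% | 74% |
| 40% | 0.5 | 0.8 | 61% | 74% |
| 40% | 0 | 0.6 | 39% | 50% |

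The first row is no dilution at all, and the documents do not rule it out.

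**4. Could an early-versus-late interaction settle it?** Power = Φ{(1 − k)/[SD × √(2/(54f) + 2/(54(1 − f)))] − 1.96}. For f = 0.4, k = 0 and SD 1.85: √(0.0926 + 0.0617) = 0.393; 1/(1.85 × 0.393) = 1.376; Φ(−0.584) = 28%. Over f = 20–50% and k = 0 or 0.5, power is about 8–29% at SD 1.85 and 10–37% at SD 1.60.

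**5. Why not stratify on it.** The seven binary factors under Sequence generation, ignoring site, already give 2^7 = 128 cells for 120 participants.

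**The case against.** **The window contradicts the rationale.** A reader might infer this from the day-4 sentence. The sentence is hedged and rests on simulations, and the same paragraph accepts treatment within seven days, which matches the outer entry limit. There is tension within the paragraph, and no contradiction with the eligibility criteria.

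**Late starters are expected to gain little.** This is not established for the randomised contrast. The Discussion's next paragraph says the inhibition needed rises from 65% to 90% or more with late start, and offers combination therapy as a response. The trial compares a combination with one of its components, so the documents do not predict a small added effect in late starters.

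**The early effect is heavily diluted and cannot be separated.** Uniform entry over seven days with no late effect would give 1 × 4/7 = 0.57 log10. That needs every participant to enter by the day-7 route, uniformly, with zero effect after day 4. One route closes at day 5, one has no onset date, and the day-7 route requires a positive test by day 5. Nor is separation impossible: onset dates are needed for eligibility, and the viral dynamic model uses the daily swabs to capture part of disease stage. That model serves EC50 estimation, however, and not the primary contrast.

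**Covariates belong in the statistical analysis plan.** Often so, and a plan not shown may include this one, in which case the point is met. But the protocol does not leave adjustment open: it names baseline load for the primary endpoint and carries that strategy over to the binary outcomes. The point improves a stated model. It also stands that the planned analysis is valid as written, since onset time is balanced in expectation.

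**Conclusion.** The point holds as one of efficiency. The primary analysis is unbiased without days since onset, but it leaves out a baseline variable that the protocol's own account makes predictive of the Day 5 load and that recruitment must collect anyway. The expected gain is roughly 2–32% of residual variance among symptomatic entrants under realistic noise, more under ideal assumptions, and less over the whole trial. These figures rest on assumed slopes, entry distribution, recall error and measurement error, none of which the documents give.

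Dilution of the average effect is possible, but its size cannot be stated from the documents. The covariate recovers precision and does not undo dilution. With 108 evaluable participants, an interaction analysis would usually leave open whether a null result meant no added effect or treatment given too late. No view is taken here on which entry window is right.

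**What to change.** Keep eligibility and the allocation factors as they are. In the statistical methods section {20a}, add days from symptom onset to first dose as a baseline covariate in both the primary mixed model and the ANCOVA. Include the symptomatic/asymptomatic indicator, and let the days term act only in symptomatic participants (a constant for the others), so that asymptomatic entrants stay in the analysis. Fix the functional form before unblinding. The first dose is taken at the baseline visit under blinded kit allocation, so the covariate cannot be influenced by arm.

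Optionally, pre-specify the treatment-by-days-since-onset interaction as supportive only. State that its power is low and that it would not by itself distinguish no added effect from treatment given too late.

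The cost is a sentence or two of analysis text and two model terms. It needs no new data and no change in sample size.

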#### Participant exclusion criteria

Exclusion criteria are as follows:Known hypersensitivity to any of the active ingredients or excipients in favipiravir, and in nitazoxanide and matched placebo.Chronic liver disease at screening (known cirrhosis of any aetiology, chronic hepatitis (e.g. autoimmune, viral, steatohepatitis), cholangitis or any known elevation of liver aminotransferases with AST or ALT > 3 X ULN).Chronic kidney disease (stage 3 or beyond) at screening: eGFR < 60 ml/min/1.73m^2^.HIV infection, if untreated, detectable viral load or on protease inhibitor therapy.Any clinical condition which the investigator considers would make the participant unsuitable for the trial.Concomitant medications known to interact with favipiravir, and with nitazoxanide and matched placebo, and carry risk of toxicity for the participant.Current severe illness requiring hospitalization.Pregnancy and/ or breastfeeding.Eligible female participants of childbearing potential and male participants with a partner of childbearing potential not willing to use highly effective contraceptive measures during the trial and within the time point specified following the last trial treatment dose.Participants enrolled in any other interventional drug or vaccine trial (co-enrolment in observational studies is acceptable).

* Considering the importance of early treatment of COVID-19 to impact viral load, the absence of chronic liver/kidney disease will be confirmed verbally by the participant during pre-screening and screening/baseline visit. Safety blood samples will be collected at screening/baseline visit (day 1) and test results will be examined as soon as they become available within 24 h.

#### Screening/baseline visit (day 1)

A delegated site staff will visit the participants at their home. After they have been given sufficient time to ask questions and provided written consent, participants will undergo a final assessment for eligibility (including a urine pregnancy test for women of childbearing potential) and will be recruited to the trial. A baseline nose swab sample for virological analysis and baseline blood samples will be taken. A baseline diagnostic nose and throat swab will be taken if the participant has not been tested for COVID-19 yet.

If they are eligible, participants will be randomised and provided with a trial medication kit, symptoms diary, containers for daily nose swab samples collection, two stool collection containers, a thermometer and instructions for taking their medications, collecting samples and recording daily body temperature readings.

Participants will be considered fully randomised once they take their first trial medication dose, witnessed by the delegated site staff. Arrangements will be made for their next trial visits.

If participants are deemed ineligible following one of the above assessments, data will still be collected on all assessments listed above apart from swab, nose swab and bloods.

The reason(s) for ineligibility will be explained to participants and any questions they have will be answered. They will be thanked for their participation and any relevant information from this will be recorded on the CRF.

If participants are deemed ineligible following results from safety bloods collected at screening/baseline visit, a delegated site research staff will contact the participant (within 6 h of results receipt) to explain the reason(s) for ineligibility and instruct them to interrupt the therapy immediately. The research staff will enquire on any adverse reactions and side effects that the participant might have experienced since starting the trial medications and record details on the screening/baseline CRF. In order to ensure the participant’s safety, arrangements for immediate collection of the medication kit from the participant’s home will be made (within 24 h), and a pills count will be performed on receipt of the medication kit at site.

